## Abstract

**Abstract:**

**Introduction:**

Selective dorsal rhizotomy (SDR) is one of the treatment options available for spasticity management in ambulatory children and young people with cerebral palsy (CYPwCP). Although improvements in gross motor function one to two years after surgery have been established, evidence of longer-term benefit requires further investigation. Given the irreversible nature of SDR and the increased rehabilitation commitments required from families and clinicians, providing evidence of longer-term benefits is essential to support their decision-making. This study aims to investigate medium (3–5 years) and long-term (6–10 years) SDR outcomes in ambulatory children with CP and how SDR affects families’ lives over time.

**Methods and analysis:**

This is a convergent parallel mixed-methods study using the International Classification of Functioning, Disability and Health as a theoretical framework. The study aims to recruit 90 CYPwCP participants, who had SDR at a tertiary hospital in the UK when aged between 3 and 14 years. Participants (parents and CYPwCP) will be invited to complete an online survey and attend the hospital for one follow-up visit 3 or more years after SDR. Comparisons will be made with existing data on objective measures and parent-reported outcomes collected in clinical practice at baseline, 6, 12 and 24 months to understand the trajectory of changes. Semistructured interviews will be conducted with 18–20 parents/carers and 25–30 CYPwCP to understand their perspectives on the outcomes of SDR compared with their prior expectations. The Framework Method will be used to analyse qualitative data both inductively and deductively. Qualitative and quantitative study data will be integrated using joint displays.

**Ethics and dissemination:**

Ethical approval has been obtained through the Coventry and Warwick Research and Ethics Committee (24/WM/0078). Findings will be shared through international conferences, peer-reviewed journals, social media and dissemination events for families and CYP.

**Trial registration number:**

NCT06518889.

STRENGTHS AND LIMITATIONS OF THIS STUDYThis mixed-methods study combines clinical outcomes with parent-reported and child-reported outcomes and experiences, prioritising the voices of children and young people with cerebral palsy.A multimodal data collection approach (online, paper, virtual and in-person) supports inclusive participation across diverse needs and contexts.Active involvement of a study advisory group of children, young people and parents with lived experience throughout design, analysis and dissemination enhances methodological rigour and relevance.The use of joint displays (convergence, divergence and silence) strengthens integration and interpretation of mixed-methods findings.Limitations include single-centre design, potential loss to follow-up due to contact changes and heterogeneity in time since selective dorsal rhizotomy and subsequent interventions, which may confound outcome attribution.

## Introduction

 Cerebral palsy (CP) is the most common physical disability with onset in childhood and has lifelong implications.^1^ It is a heterogeneous condition with varied clinical presentations that affect movement, posture and coordination, often leading to limitations in activity and participation.^2^ Spasticity is the most common neurological feature, affecting 70% of children and young people with CP (CYPwCP).^3^ Management typically focuses on reducing spasticity through a range of interventions, including oral medications, botulinum toxin A injections and neurosurgical interventions.^4^ Rehabilitation therapy remains the primary adjunct to optimise outcomes from these treatment approaches.^5^

Selective dorsal rhizotomy (SDR) is a neurosurgical procedure used to permanently reduce lower limb spasticity in CYPwCP. In the single-level approach, sensory nerve roots from L1 to S2 are identified and divided into rootlets. Approximately 60%–70% of sensory rootlets between L2 and S1 and 50% of the L1 sensory rootlets are selectively divided.^6^ SDR is typically offered to CYPwCP classified as Gross Motor Function Classification System (GMFCS) levels II and III,^7^ who are able to walk with or without walking aids. Surgery is followed by intensive rehabilitation for at least 2 years to optimise functional outcomes.^8^ The SDR procedure has been available at some centres around the world for over four decades, but was only commissioned by the National Health Service in England (NHSE) in 2018 for CYPwCP in GMFCS levels II and III, following a multicentre study.^9^ Under current NHSE guidelines, CYPwCP are only followed for 2 years after SDR and then discharged to their local community care without provisions for long-term monitoring. As these CYPwCP have not yet reached skeletal maturity, they remain at risk of developing deformities requiring further orthopaedic interventions.^10^ As such, the evidence on the longer-term outcomes of SDR within the UK healthcare context is lacking.

Short-term outcomes of SDR, up to 2–3 years after surgery, are well-established, particularly in reducing spasticity and improving gross motor function.^11 12^ However, evidence for longer-term benefits in gross motor function and participation remains inconclusive, as highlighted in a recent systematic review.^13^ Despite the lack of clear evidence for longer-term benefits of SDR over other interventions, SDR continues to be offered at various centres worldwide, supported by findings from long-term observational studies using a variety of outcome measures.^14 15^ In shared decision-making, clinical decisions regarding the suitability of the SDR procedure occur alongside families’ expectations. Parental decision-making is frequently influenced by hopes of long-term benefits such as reduced orthopaedic interventions and improved quality of life (QoL).^16^ This has also been a strong focus from our patient and public involvement (PPI) activities. Families regularly express the need for clearer information on longer-term outcomes to guide their decision-making.^16^

Long-term outcomes following SDR have been identified among the top 10 research priorities in both the Childhood Disability and Paediatric Lower Limb Surgery James Lind Alliance Priority Setting Partnerships.^17 18^ There is a knowledge gap in the evidence on the effects and impact of SDR on CYP’s physical functioning and QoL within the UK healthcare context in the medium to longer term. Under the current NHSE SDR pathway, CYPwCP are seen for up to 2 years at a specialist centre, after which care is managed by local community services.^9^ Currently, there is no national CP register in the UK to capture the longer-term outcomes of CYPwCP who have undergone SDR. Furthermore, CYPs and parents’ experiences, prior expectations and perceptions of outcomes of SDR and rehabilitation remain underexplored. Capturing the voices of CYPs and parents is central to strengthening the evidence base and better supporting their needs, and informing their decision-making and expectations.

### The MOSAiC study

This paper describes the protocol for a mixed-methods study in an established tertiary paediatric movement disorder service in London, UK. The aims of this study are (1) to investigate medium (3–5 years) to long-term (6–10 years) outcomes after SDR surgery in ambulatory children with CP and (2) to explore how SDR surgery affects families’ (CYPs and parents’) lives over time. The study will address three main research questions:

What are the gross motor function, musculoskeletal and QoL outcomes 3–10 years after SDR in ambulatory CYPwCP?What are CYPs’ and parents’ experiences of SDR and rehabilitation 3–10 years after SDR in relation to their prior expectations and subsequent outcomes?How do gross motor function, orthopaedic and QoL outcomes in ambulatory CYPwCP compare with CYP and their parents’ perceptions, experiences and QoL 3–10 years after SDR surgery?

## Methods

### Study design and theoretical framework

MOSAiC (**M**edium to longer term **O**utcomes following **S**elective dorsal rhizotomy in **A**mbulatory children w**i**th **C**erebral palsy) is an observational study using a mixed-methods convergent parallel study design, in which quantitative and qualitative data will be collected concurrently, analysed separately and then integrated and synthesised.^19^ The quantitative component (phase 1) comprises an observational cohort study, involving a survey and clinical assessments to objectively assess changes in gross motor function compared with baseline and previous assessments. The qualitative component (phase 2) involves semistructured interviews with CYPwCP and parents to explore their perspectives on the outcomes and lived experiences following SDR surgery (figure 1). The integration and synthesis of findings from both phases will bring new insights by leveraging the strengths of both methodologies.^20^ This dual approach is designed to generate a more comprehensive and holistic understanding of longer-term SDR outcomes, guided by the International Classification of Functioning, Disability and Health (ICF)^21^ as a theoretical framework. The ICF is a biopsychosocial model of functioning and disability and will underpin all aspects of this study, including study design, data collection, analysis and interpretation.

**Figure 1 F1:**
[figure not shown]
Mixed-methods study design. CYP, children and young people; GOSH, Great Ormond Street Hospital for Children; SDR, selective dorsal rhizotomy.

The study is philosophically grounded in pragmatism, which supports pluralistic approaches to knowledge generation by incorporating both subjective and objective perspectives.^22^ Consistent with this paradigm, equal priority will be given to both the quantitative and qualitative methodologies. The integration of these two components will occur at the data collection, results and analysis stages. A nested subsample from phase 1 will be purposefully selected for phase 2 interviews. The initial group-level and individual-level findings will further inform the development of the interview topic guide. Final interpretation will be derived through the synthesis of findings from both phases.

### Study sample and recruitment

This single-centre study will be conducted at Great Ormond Street Hospital for Children (GOSH), a paediatric tertiary hospital in London, UK. Inclusion criteria are CYPwCP who had SDR surgery at GOSH at least 3 years prior and were classified as GMFCS level II or III at the time of surgery. The GMFCS is a five-level ordinal classification system that categorises CYPwCP based on gross motor abilities, mobility limitations, need for assistive devices or wheeled mobility.^7^ Children in levels I and II are able to walk independently with some difficulty, while those at level III walk using a walking aid (online supplemental SI-1). The NHS England selection criteria for SDR eligibility are outlined in online supplemental SI-2. Participants will be eligible for this study if they completed a baseline assessment prior to SDR and have at least one follow-up assessment at 6, 12 or 24 months postsurgery. Parents of eligible CYPwCP will also be invited to participate. For those who have recently undergone orthopaedic surgery or received botulinum toxin injections in the lower limbs, data will be collected 3–9 months after that procedure, allowing time for recovery. This decision will be based on the type of procedure and in consultation with CYPwCP and their families, consistent with routine practice.

Based on the eligibility criteria, a minimum of 182 participants has been identified from the GOSH SDR database for inclusion in the observational cohort study (phase 1). All CYPwCP and parents participating in phase 1 will be eligible for the qualitative study (phase 2). Purposeful sampling will be used to identify CYPwCP and parents, ensuring a diverse representation of participants based on the GMFCS level, age at surgery, length of follow-up and outcomes at 2 years after SDR. The concept of ‘information power’, where the more relevant and high quality information the sample holds, the lower the number of participants needed, is used to determine the sample size.^23^ Based on this premise and previous qualitative research experience, a sample of approximately 18–20 parents and 25–30 CYPwCP is anticipated to provide maximum variation and depth to explore a range of experiences and perspectives.

### Recruitment process

All families attending the clinical service at GOSH who have previously agreed to be contacted for research will receive an invitation via email or post. A member of the clinical team will approach families and CYPwCP to confirm their interest in the study. If they agree to be contacted, the principal investigator (PI) (DC) will provide further study information. Families who agree to take part in the study will receive personalised survey links for both parents and CYP and will be invited to attend a face-to-face appointment at GOSH.

For the qualitative component (phase 2), a separate participant information sheet will be provided to eligible parents and CYP. Written informed consent will be obtained from parents, and consent or assent (as appropriate) from CYPwCP before data collection for both phases.

### Procedures

#### Phase 1: quantitative study

Participants (parents and CYPwCP) will complete an online survey via REDcap, followed by a single study visit for a clinical assessment. The clinical assessment will start with more physically demanding assessments, such as the 6-Minute Walk Test (6-MWT),^24^ Gross Motor Function Measure (GMFM),^25^ Timed Up and Go (TUG),^26^ followed by evaluation of muscle tone using the Modified Ashworth Scale (MAS)^27^ and lower limb passive joint range of movement. The assessment protocol mirrors standard clinical practice, and all participating CYPwCP will be familiar with this process. All assessments will be conducted by the PI (DC), supported by a clinical physiotherapist or physiotherapy assistant.

The outcomes and outcome measures were selected based on the findings from a scoping review on the outcomes used in the SDR literature,^28^ NHSE commissioning guidelines and acceptability and meaningfulness to parents and CYPwCP (as informed by the PPI and study advisory group). The selected outcomes and measures are presented in table 1 and the mapping of outcomes across the domains of the ICF is illustrated in figure 2.

**Table 1 T1:** Outcomes measures included in this study

	Measure	Administration
Classification	Gross Motor Function Classification System–Family report Questionnaire	Questionnaire
Primary outcome measures	Gross Motor Function Measure-66 and centiles	Clinician-assessed
	6-Minute Walk Test	Clinician-assessed
	Cerebral Palsy Quality of Life	Questionnaire–Parent-proxy and CYP-reported
	MOSAiC Study Questionnaire	Questionnaire–Parent-reported
Secondary outcome measures	Modified Ashworth Score	Physical examination
	Timed Up and Go	Clinician-assessed
	Edinburgh Visual Gait Analysis	Clinician-assessed
	Gait Outcome Assessment List–Child Version	Questionnaire–CYP-reported, with assistance from parent carer, if needed
	Functional Mobility Scale	Questionnaire–Parent and CYP-reported
	Functional Assessment Questionnaire	Questionnaire–Parent-reported

CYP, children and young people; MOSAiC, Medium to longer term Outcomes following Selective dorsal rhizotomy in Ambulatory children with Cerebral palsy.

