#### Secondary Outcome Measures

MAS: The MAS is a widely used clinical tool for assessing muscle tone by measuring resistance to passive movement during a high-velocity stretch.^27^ The limb is moved through its available range of motion, and resistance is graded on a 6-point ordinal scale, from 0 (no increase in tone) to 4 (rigid limb). The scale includes an intermediate score of 1+to capture subtle increases in tone. The inter-rater agreement has been reported with a mean ICC of 0.686 (95% CI 0.563 to 0.780) and a kappa coefficient (κ) of 0.360 (95% CI 0.241 to 0.468). The intrarater agreement shows an ICC of 0.644 (95% CI 0.543 to 0.726) and a κ of 0.488 (95% CI 0.370 to 0.591).^40^ The MCID for MAS in CYPwCP has not been established.

TUG: The TUG is a functional mobility test used to evaluate dynamic balance and anticipatory postural adjustments in CYPwCP.^26^ Participants are instructed to rise from a chair, walk 3 m to touch the wall and return to sit down as quickly as possible, without running. Usual walking aids and orthoses are used as needed. The TUG has excellent inter-rater reliability (ICC: 0.83–0.99).^41^ Minimal detectable change values range from 1.40 to 8.74 s, and MCID estimates range from 0.22 to 5.31 s in children aged 3 to 10 years.^41^

Edinburgh Visual Gait Analysis (EVGS): The EVGS is a video-based observational tool used to assess gait deviations in CYPwCP.^42^ It consists of 17 gait parameters measured at six anatomic levels (foot, ankle, knee, hip, pelvis and trunk) representing key features of pathological gait in CYPwCP. Each parameter is scored on a 3-point ordinal scale (0=normal, 1=moderate deviation, 2=marked deviation), resulting in a total score ranging from 0 (normal gait) to 34 (maximal deviation). The EVGS has excellent inter-rater (ICC2,1=0.90–0.97) and intrarater (ICC2,1=0.91) reliability.^43^ There is a large variation in the MCID values reported in the literature, ranging from 2.4 to 15 points. The MDC^90^ of 6.0^43^ and the MCID of 2.4 points^44^ have been proposed.

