#### Phase 1: quantitative data analysis

Descriptive analysis will be used to provide participants’ demographic and baseline characteristics. Continuous variables will be summarised using mean and SD when normally distributed, or median and IQR when skewed. Categorical variables will be presented as frequencies and percentages. Association between categorical variables will be examined using cross-tabulation and χ² tests. The primary and secondary outcome measures (GMFM-66, GMFM-66 centile scores, 6-MWT, CP QOL, TUG, FMS and FAQ) will be compared between baseline and subsequent follow-up time points. Generalised linear equation models will be used to analyse longitudinal data across multiple time points. Univariate analysis will be conducted to explore associations between individual predictors and outcome variables. Non-parametric tests will be applied to ordinal outcome measures (FMS, FAQ and SMC). A multiple regression model will be created to identify predictors of favourable outcomes, incorporating relevant covariates.

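### For the observer-scored GMFM-66, the PI makes all late assessments, while the earlier assessors and access to earlier scores are not described, so a rater difference or anchoring could pass for late change

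*Protocol article*

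**What the plan says.** The section on Procedures, Phase 1: quantitative study, has participants complete a survey, "followed by a single study visit for a clinical assessment". The visit covers the 6-MWT, GMFM, TUG, MAS and passive joint range. On who does this, the text reads "All assessments will be conducted by the PI", "supported by a clinical physiotherapist or physiotherapy assistant". It adds that the visit follows the usual clinic routine.

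The Abstract gives the reference data: "Comparisons will be made with existing data on objective measures and parent-reported outcomes collected in clinical practice at baseline, 6, 12 and 24 months". Under Phase 1: quantitative data analysis, the listed outcomes (GMFM-66 and its centiles, 6-MWT, CP QOL, TUG, FMS and FAQ) "will be compared between baseline and subsequent follow-up time points".

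Under Study sample and recruitment, interviewees are chosen on, among other things, "length of follow-up and outcomes at 2 years after SDR".

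The article does not name the assessors of the baseline to 24-month visits. It does not say whether the PI sees a child's earlier scores before the late visit, and it describes no second scorer or agreement check. The limitations listed after the Abstract and in the Discussion cover the single centre, loss to follow-up, heterogeneity and later interventions, the lack of a comparison group and sampling bias. They do not cover the assessor.

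**The concern.** The quantitative answer on late outcome rests on a before-and-after contrast within each child. The late side of that contrast comes from one person. The early side comes from routine clinics with unnamed assessors. If those assessors were other people, the rater changes just where the late period begins. No group assessed concurrently by the PI could then separate a rater difference from a real change. If the PI has seen the earlier scores, a second route opens: a judgement can be drawn towards the last recorded value, which would tend to look like a maintained gain.

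The measure most exposed is the GMFM-66, a primary outcome built from 66 items that an observer grades 0 to 3. Its quoted MCIDs are small, 1.5 units at GMFCS level II and 1.2 at level III, so a modest consistent difference in scoring would matter. Such a difference moves every child the same way and does not shrink as the sample grows.

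**Working it through.** **Which outcomes are exposed.** Taken from Table 1, the outcome descriptions and the list of baseline comparisons:

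| Outcome | Exposure |
|---|---|
| GMFM-66 and centiles (primary) | Observer-scored at the visit and compared with baseline: exposed |
| 6-MWT (primary), TUG (secondary) | Metres and seconds: less exposed |
| CPQOL, MOSAiC questionnaire, GOAL, FMS, FAQ | Parent- or CYP-reported: not scored by the PI |
| MAS (secondary) | Graded at the visit but not in the list of baseline comparisons: exposed only if so compared |
| EVGS (secondary) | Video-based, scorer not stated, not in that list: exposed only if so compared and scored by the PI |

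**Reliability figures.** The only GMFM-66 figure quoted is a test–retest ICC of 0.99, which does not address a change of rater. Suppose a between-child SD of 8 to 12 units (my assumption). The standard error of measurement is SD × √(1 − 0.99), or 0.8 to 1.2 units. The random error of a difference is SD × √0.02, or 1.13 to 1.70 units. Averaged over 90 children this is 1.13/9.487 = 0.12 to 1.70/9.487 = 0.18. Random error therefore averages out, but a constant shift does not.

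For the MAS, the article says "The inter-rater agreement has been reported with a mean ICC of 0.686", against 0.644 within rater. The kappas run the other way: 0.360 between raters (95% CI 0.241 to 0.468) and 0.488 within (0.370 to 0.591), with overlapping intervals. These figures do not show that changing rater is clearly worse than keeping the same one, so the point does not rest on them.

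**Scale of a constant shift.** The article gives no SD of change and no derivation of the 90, so there is no stated figure to reproduce. Inputs:
- n = 90, the recruitment target in the Abstract, taking every child to contribute a pair of scores;
- shift b = 1.2 or 1.5 units, the quoted MCIDs used only as a yardstick, and 0.5 as a smaller case;
- SD of change 4, 6 or 8 units, assumed.

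Formulas: SE = SD/√90, with √90 = 9.487. With true change zero, the probability of a two-sided 5% result is Φ(b/SE − 1.96) + Φ(−b/SE − 1.96).

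- SD 4: SE = 4/9.487 = 0.422; 1.2/0.422 = 2.8 standard errors
- SD 6: SE = 6/9.487 = 0.632; 1.2/0.632 = 1.9 standard errors
- SD 8: SE = 8/9.487 = 0.843; 1.2/0.843 = 1.4 standard errors

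Probability of a nominally significant change when there is none:

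| Shift | SD 4 | SD 6 | SD 8 |
|---|---|---|---|
| 0.5 | 0.220 | 0.124 | 0.091 |
| 1.2 | 0.812 | 0.475 | 0.296 |
| 1.5 | 0.945 | 0.660 | 0.428 |

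The table shows what a shift would do. It is not evidence that a shift of any of these sizes exists.

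**The case against.** **The change of rater is conjecture.** The article does not say that the assessors changed. The PI may have made some or all of the earlier assessments. This stands, and the point has to be conditional. If the PI made them all, the rater route disappears and only anchoring or expectation remains.

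**Access to earlier scores is not established.** A reader might infer from the use of 2-year outcomes in interview sampling, and of individual findings in the topic guide, that the PI scores late visits knowing the earlier results. The documents do not support that. They do not say who does the sampling, and the topic-guide text describes findings passing from phase 1 to phase 2. Phase 1 visits began in June 2024 and interviews run from July 2025, so many visits may come before any sampling. The full protocol may provide for masking.

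**One late assessor has advantages.** It removes between-rater variation within the late wave, which helps a comparison of 3–5 with 6–10 years. The mirrored clinic routine and the standardised 6-MWT instructions also help. They standardise the procedure, however, and not the grading of GMFM items.

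**The size is assumed on both sides.** Neither the shift nor the SD of change comes from the article. This stands, and the figures are for scale only.

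**An assessor sensitivity analysis is commonly left to the SAP.** That is fair as to its detail. But the article itself fixes a sole late assessor and lists its limitations without mentioning this one.

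**Conclusion.** The concern holds in a conditional form, for the clinician-assessed outcomes and chiefly the primary GMFM-66. The article fixes the PI as the late assessor, sets those scores against routine-clinic scores without a control group, and is silent both on who scored earlier and on whether earlier scores are withheld. A rater difference (if earlier raters differed) or anchoring (if earlier scores were seen) is therefore a possible explanation for late change or for maintained gain, and a larger sample would not remove it. Its size is unknown. With 90 pairs and an assumed SD of change of 4 to 8 units, a 1.2-unit shift would be 2.8 to 1.4 standard errors.

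A reader might go further and infer that every late outcome is affected, or that assessor effect and true change cannot be told apart at all. The documents support neither. The questionnaires are not scored by the PI, timed and measured tests are less exposed, MAS and EVGS are not among the stated baseline comparisons, and separation fails only if the earlier raters were other people or the earlier scores were seen. This is a worthwhile, inexpensive improvement and not a demonstrated bias.

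**What to change.** 1. For visits still to come before the stated October 2025 close, have the PI score and lock the GMFM-66 (and MAS) in REDCap before opening that child's earlier scores. This changes only the order of work. It cannot help visits already done, and it does not remove the PI's knowledge that every child had SDR.
2. Extract from the clinical record who made each baseline to 24-month GMFM-66 assessment. As a sensitivity analysis, report late change separately for children whose earlier assessor was the PI and for those assessed by someone else, or adjust for assessor. This costs one field from existing records and one table, needs no extra assessor, and can be done after data collection closes. Assessor identity may be missing for some visits and the same-assessor group may be small. If the PI made none of the earlier assessments, the analysis cannot separate rater from time, and that should be stated.
3. Add the assessor issue to the limitations: who made the earlier assessments, and whether earlier scores were withheld at the late visit.
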